**Objective:**

This study aims to report the impact of POCT for influenza on antimicrobial prescribing in primary care. We will additionally describe severe outcomes of infection (hospitalization and mortality) and how POCT is integrated into primary care workflows.

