**Results:**

We will present the crude and adjusted odds of antimicrobial prescribing (all antibiotics and antivirals) given a POCT diagnosis of influenza, stratifying by whether individuals have a respiratory or other relevant diagnosis (eg, bronchiectasis). We will also present the rates of hospital referrals and deaths related to influenza infection in PIAMS study practices compared with a set of matched practices in the sentinel network and the rest of the network. We will describe any difference in implementation models in terms of staff involved and workflow.

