### Objectives

This study aims to report the impact of POCT for influenza on antimicrobial prescribing in primary care. We will additionally describe severe outcomes postinfection (hospitalization and mortality) and how POCT is integrated into primary care workflows.

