Antimicrobial prescribing and other study outcomes for those who have been swabbed will be obtained by linking information from the cobas Liat analyzer with data from the patient’s computerized medical record in primary care. We will demonstrate the feasibility of reporting antimicrobial stewardship and severe outcomes postinfection. Severe outcomes postinfection such as hospitalization and mortality will be obtained by linking the patient’s primary care computerized medical record to secondary care records at the national level including hospitalization and mortality data. A recent study used a linked cohort to study severe outcomes from COVID-19 infection [25].

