To answer our secondary objective, we will select a matched set of practices from the rest of the English national sentinel network based on practice size, average age of registered patients, proportion of registered female patients, and number of GPs employed during the study.

The rates of hospital referrals and deaths related to influenza infection within 30 days of diagnosis will be compared between PIAMS study practices and the rest of the network using the ANOVA test.

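### The severe-outcome objective is hospitalization and mortality, but the only planned between-practice comparison names hospital referrals, an undefined term that need not mean admission

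*Protocol article*

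**What the plan says.** The Objectives section states the aim: "We will additionally describe severe outcomes postinfection (hospitalization and mortality"). The abstract's Objective paragraph says the same, and the Introduction's rationale and the Discussion's Overview also pair hospitalization with mortality.

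The section on face-to-face recruitment gives the data source: "Severe outcomes postinfection such as hospitalization and mortality will be obtained by linking" the primary care record "to secondary care records at the national level including hospitalization and mortality data".

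The analysis appears in two places. Under Statistical Methods, for the secondary objective: "The rates of hospital referrals and deaths related to influenza infection within 30 days of diagnosis will be compared" between study practices and the rest of the network. In the Results paragraph of the abstract: "We will also present the rates of hospital referrals and deaths related to influenza infection in PIAMS study practices", set against matched practices and the rest of the network.

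The article does not define hospital referral. It does not say that the term stands for admission, and it plans no other between-practice comparison of a hospital outcome.

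**The concern.** A referral and an admission are different events. In ordinary primary-care use, a referral is something the clinician does and an admission is something that happens to the patient. A referred patient may be assessed and sent home. A patient who worsens after the consultation may be admitted by ambulance or through an emergency department with no referral from the practice. Later deterioration of that kind is part of what a 30-day severe-outcome window is there to capture.

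The exposure adds a second difficulty. In study practices the result reaches the clinician in under 20 minutes and nobody is blinded, so the test can change the decision to refer without any change in how ill the patient becomes. Comparator practices are described as using the usual virology sampling programme.

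A difference in referral rates could therefore reflect clinician behaviour, in either direction, and be reported as a difference in severe outcomes. The Introduction says the effect of point-of-care testing on hospitalization and mortality has not been reported, and the Conclusion expects the study to inform larger studies of severe outcomes. A referral comparison would not supply the hospitalization part of that evidence.

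**Working it through.** The plan states no figure for this outcome (no expected rate, event count or power), so there is nothing to reproduce. The check is a comparison of texts.

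| Place in the protocol article | Hospital component | Death component |
|---|---|---|
| Abstract, Objective | hospitalization | mortality |
| Introduction, rationale | hospitalization | mortality |
| Objectives | hospitalization | mortality |
| Face-to-face recruitment section (data source) | hospitalization, linked national records | mortality, linked national records |
| Abstract, Results | referrals | deaths |
| Statistical Methods, secondary objective | referrals | deaths |
| Discussion, Overview | hospitalization | mortality |

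Three things follow.

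1. The death component agrees throughout. Only the hospital component changes.
2. The change occurs in both places that describe the comparison, so it is not a single slip.
3. The list of adjustment covariates, just before the secondary analysis, counts prior hospitalizations. The article uses the admission term there and a different term for the outcome.

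The possible size of the problem can only be illustrated, because the inputs are not in the documents. Let A be the admission rate, s the share of admissions reached through a GP referral, and f the fraction of referrals that end in admission. Then

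referral rate = A × s / f.

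If A and f are the same in both groups of practices, the apparent rate ratio is s(study) / s(comparator), although the true admission ratio is 1. Assume a comparator share between 30% and 90%, and a shift of 10 percentage points either way in study practices:

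| Assumed comparator share s | Admissions missed, 1 − s | Ratio if share falls by 0.10 | Ratio if share rises by 0.10 |
|---|---|---|---|
| 0.30 | 0.70 | 0.20/0.30 = 0.67 | 0.40/0.30 = 1.33 |
| 0.50 | 0.50 | 0.40/0.50 = 0.80 | 0.60/0.50 = 1.20 |
| 0.70 | 0.30 | 0.60/0.70 = 0.86 | 0.80/0.70 = 1.14 |
| 0.90 | 0.10 | 0.80/0.90 = 0.89 | 1.00/0.90 = 1.11 |

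The table shows that the mechanism can work in either direction. It does not estimate what would happen in this study.

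**The case against.** The strongest reply is that the authors may have used referrals loosely for the linked hospitalization outcome. The analysis sentence sits in a paragraph group that opens by addressing the secondary objective, the data source for severe outcomes is stated elsewhere, and no passage assigns the comparison to GP-coded referrals. On that reading no admissions are lost and the fault is one imprecise word. This is plausible and cannot be excluded. It does not remove the point: the wording still conflicts with the objective and needs the same correction.

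A reader might infer more than the text supports:

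- **That admissions without a referral are certainly lost, or that the linked data are certainly left unused.** The analysis sentence names no data source, so both statements depend on the literal reading of referral.
- **That a specific artefact can be expected.** For example, a fall in the referred share from 50% to 30% would give an apparent 40% reduction (1 − 0.30/0.50 = 0.40). That figure only restates the assumed shift, and nothing in the article says that testing lowers the referred share.
- **That linkage is part of the objective.** The objective is hospitalization and mortality; linkage is the stated source of the data.
- **That no new data are needed.** The linkage is described in the recruitment section, straight after a sentence about people who were swabbed. The article does not expressly extend it to comparator practices.

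It is also fair to say that admissions are not wholly independent of the test. Those reached through a GP referral still depend on a decision made with the result in hand. Admissions are less directly affected than referrals, not immune.

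Finally, this is a secondary, largely descriptive aim in a nonrandomized study of 10 practices, and the article acknowledges the design limitation. That lowers the priority of the point, but the contradiction remains.

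**Conclusion.** The point holds as a contradiction within the article. The objective and data source name hospitalization; the only stated between-practice comparison names hospital referrals. Taken literally, the hospital component of that comparison would measure a clinician's decision that the unblinded result can influence, and would not answer the stated objective. If admissions were intended, the analysis wording is wrong.

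Confidence in the conflict of terms is high. The bias mechanism rests on the ordinary meaning of an undefined term, and its size cannot be computed from the documents; the ratios shown are illustrations under assumed shares.

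The point should be corrected but is not critical. It affects one of the two components of a secondary objective. The mortality component and the primary prescribing outcome are untouched.

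**What to change.** In the secondary-objective paragraph of Statistical Methods and in the Results paragraph of the abstract, replace hospital referrals with hospital admissions within 30 days by any route, taken from the linked national records already described. State that admissions are ascertained in the same way in study and comparator practices. If referrals are kept, define them and report them separately as a process measure, not as a severe outcome.

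The text change is small. Two costs need checking:

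- Linkage must be confirmed for the comparator practices.
- Waiting for linked data may delay the analysis. Recruitment runs to May 2023 and the outcome window is 30 days, so the last patients' follow-up could run well into June 2023, the month by which the final analysis is due.

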## Methods

### Study Setting and Population

The impact of POCT for influenza on antimicrobial stewardship (PIAMS) study will take place between December 2022 and May 2023, during the influenza season as defined by the UK Health Security Agency (UKHSA). It is nested within the English national sentinel network managed by the Oxford-Royal College of General Practitioners (RCGP) Research and Surveillance Centre (RSC) at the Nuffield Department of Primary Care, University of Oxford. This network of over 1800 primary care practices is the primary infectious disease surveillance network for England, which is generally representative of the English population [19]. It has been providing weekly infection data for over 50 years that are used to monitor trends in infectious disease and investigate real-world vaccine and treatment effectiveness [20].

All practices that contribute data to the English national sentinel network will be invited to participate in the PIAMS study, and 10 practices will be selected to take part in the PIAMS study. We will prioritize practices within the network with capacity to undertake influenza POCT and who had previously been involved in SARS-CoV-2 POCT through the RAPTOR-C19 study [21]. Those practices that have a history of less than 80% complete data returns during the previous winter season will be excluded.

Each participant practice will receive training about the study, including hands-on training on how to administer a swab test and how to use the POCT analyzers.

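### ANOVA is poorly suited to comparing rare 30-day hospital referrals and deaths between 10 practices and a network of over 1800, and the stated test does not match the comparator and endpoint given elsewhere

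*Protocol article*

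**What the plan says.** In the protocol article, Statistical Methods opens the secondary analysis with "To answer our secondary objective, we will select a matched set of practices from the rest of the English national sentinel network", matching on practice size, average patient age, proportion of female patients and number of GPs. The next sentence gives the outcome, "The rates of hospital referrals and deaths related to influenza infection within 30 days of diagnosis", and says that these rates "will be compared between PIAMS study practices and the rest of the network using the ANOVA test". The matched set does not appear in that sentence. The unit of analysis (patient or practice) is not stated.

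Other parts of the article bear on this:

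- **Comparator.** The Results paragraph of the Abstract says that the same rates will be shown "compared with a set of matched practices in the sentinel network and the rest of the network".
- **Endpoint.** The Objectives section says "We will additionally describe severe outcomes postinfection (hospitalization and mortality". The section on face-to-face recruitment and testing says that hospitalization and mortality will come from linked secondary care records. The Abstract's Results paragraph and Statistical Methods speak of hospital referrals.
- **Size.** Study Setting and Population says "10 practices will be selected to take part in the PIAMS study" and describes the network with "This network of over 1800 primary care practices".

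**The concern.** Three things do not fit together.

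1. ANOVA relies on roughly normal data with a common variance. With a few events spread over 10 practices, practice rates are mostly zero or one event over a small denominator. Their variance depends on the number of cases each practice records. With over 1800 practices on the other side, the pooled variance is essentially the comparator's variance, so the test is calibrated only if PIAMS practices happen to have similar case counts.
2. Matched practices are selected for this objective, yet the only stated test does not use them.
3. A referral is not an admission, and the linkage described yields admissions.

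The study is meant to inform larger studies of effectiveness and severe outcomes. A p-value on hospital events and deaths that depends on how many cases comparator practices happen to record could mislead their design.

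**Working it through.** **No plan figure to reproduce.** The article gives no event rate, sample size or power for severe outcomes. Its one sample size (1023) concerns antibiotic prescribing and does not bear on this point. All risks below are assumptions.

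**Expected events in PIAMS practices**

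- Swabs: 10 practices × 3 per week × 26 weeks (December to May) = 780, up to the stated maximum of 1000.
- Influenza share: 215/818 = 26.3% (Table 1) to 36% (Abstract). These are shares of positive swabs, used as a proxy. Positivity among all swabs would be lower.
- Cases: 780 × 0.263 = 205 to 1000 × 0.36 = 360, or about 20 to 36 per practice.
- Hospital events = cases × risk: 1.0-1.8 at 0.5%, 2.1-3.6 at 1%, 4.1-7.2 at 2%, 10-18 at 5%.
- Deaths at an assumed 0.1%: 0.2-0.36, with a 70-81% chance of none.

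**Why the error rate depends on case counts.** Take practice-level rates, risk p, and m_P and m_R cases per practice in PIAMS and the comparator. The pooled variance is approximately p(1−p)/m_R, because 1800 practices dominate it. The true variance of a PIAMS practice rate is p(1−p)/m_P. The effective critical value is therefore 1.96 × √(m_P/m_R):

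- 26 vs 26: 1.96, error 5%.
- 26 vs 100: 1.96 × √0.26 = 1.00, error about 32%.
- 26 vs 8: 1.96 × √3.25 = 3.53, error about 0.04%.

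With intra-practice correlation ρ, replace 1/m by [1 + (m−1)ρ]/m. At ρ = 0.02 and 26 vs 100: 1.5/26 = 0.0577 and 2.98/100 = 0.0298, so 1.96 × √(0.0298/0.0577) = 1.41, error about 16%.

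**Simulation** (one-way ANOVA on practice rates, 10 vs 1800 practices, equal true risk of 0.5% to 5%, nominal 5%, 4000 replicates per setting):

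| Cases per practice (PIAMS vs rest) | Rejections, ρ = 0 | Rejections, ρ = 0.02 |
|---|---|---|
| 26 vs 26 | 4.0-4.9% | 4.2-5.0% |
| 26 vs 100 | 28-42% | 8-15% |
| 26 vs 8 | 0.1-0.3% | 0.4-1.2% |

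Other runs of the four-fold case gave 23-40% (ρ = 0), 6-16% (ρ = 0.02), and 13-43% over a further range of assumptions. The direction is stable and the exact figure is not. If ANOVA were run on patient-level 0/1 data instead, the error is 3-5% without clustering and about 5-12% at ρ = 0.02.

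**Ability to show a benefit.** With equal counts and no true difference, rejections in the direction of fewer events in PIAMS practices occurred in 0% of runs at 0.5% and 1% risk, and in at most 0.6% at 2%, against a nominal 2.5%. The reason is arithmetic. At 1% risk and 26 cases per practice, the standard error of the PIAMS mean is √(0.01 × 0.99/260) = 0.0062, and 1.96 × 0.0062 = 0.012. That exceeds 0.01, so even zero events in all 10 practices is not significant. With a true halving, the correct-direction rejection rate was 0% at 1% risk. At 2% risk it was 8% (ρ = 0) or 0.7% (ρ = 0.02).

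**Text side by side.** For the comparator, the Statistical Methods test names the rest of the network only, while the Abstract names matched practices and the rest. For the endpoint, the Abstract's Results paragraph and Statistical Methods name referrals, while the objectives and the linkage text name hospitalization.

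**The case against.** The strongest defence has four parts.

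- **Role.** Severe outcomes are secondary and are to be described. The Limitations section concedes the nonrandomized design and leaves health outcomes to a later experimental study. No power is claimed, and the primary logistic analysis is untouched. This stands, and it lowers the severity.
- **Validity is conditional.** With equal case counts ANOVA holds close to 5%. No comparator case counts are given. Because the Introduction says few patients with respiratory infection are tested routinely, PIAMS practices may well record more confirmed cases, which makes the test conservative. This stands too. A reader might infer that ANOVA is invalid outright or will produce false positives, but the documents support neither. They do leave the error rate uncontrolled.
- **Matched practices.** A reader might infer that the matched practices go unused in the study. The Abstract names them as a comparator, and three groups would be a natural reason to name ANOVA. They are absent only from the stated test.
- **Information.** A better model creates no events. At 1% risk the chance of 0 events in 260 is 0.99^260 = 7%, so an exact test would not flag a benefit there either. This stands. The gain from another model is a controlled error rate and an honest interval, not power.

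Model details can be left to an analysis plan that is not shown. The article does, however, commit to a named test and comparator, so the choice itself is open to comment.

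**Conclusion.** The point holds as a should-fix on the secondary objective. ANOVA is poorly suited to these outcomes. On practice-level rates its error rate is near 5% with equal case counts, about 1% or less when comparator practices record about a third as many cases, and well above 5% when they record about four times as many (roughly 13-43%, or 6-16% at ρ = 0.02). At risks of 2% or less it has almost no ability to flag a benefit. These figures rest on assumed risks of 0.5-5%, assumed case counts and practice-level analysis, none of which the article states. The expectation of few events (1 to 7 hospital events) holds at risks up to about 2% among swabbed influenza-positive patients. It does not hold at 5%, or if cases include unswabbed patients with a recorded diagnosis.

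The two textual mismatches need no assumption: Abstract and Statistical Methods disagree on the comparator, and referrals are analysed where hospitalization is the objective.

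**What to change.** In Statistical Methods:

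1. State the unit of analysis and how an influenza case is defined in comparator practices, so that each rate has a denominator.
2. Replace ANOVA with a count or binary model that uses case denominators and accounts for practice clustering: Poisson or negative binomial with a log-denominator offset, or logistic GEE with a small-sample correction. Use exact or penalised methods for deaths.
3. Make PIAMS versus matched practices the main contrast and the rest of the network supportive, and word the Abstract and Statistical Methods alike.
4. Use hospitalization from linked records as the endpoint throughout, after confirming that the linkage covers comparator practices.
5. Report events, denominators, rate ratios and 95% intervals as descriptive, in line with the Objectives. For illustration, 3 events in 263 cases is 1.1% (exact 95% CI 0.2% to 3.3%), and 0 in 263 has an upper limit of 1.4%.

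The cost is a change of wording and slightly more analysis work, with no new patients. The intervals will be wide, which is what the data can support.

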### Ethical Considerations

The study was approved by the English National Research Ethics Committees (Integrated Research Application System reference: 292961; REC reference: 21/YH/0077).

A practice GP or research nurse will undertake informed consent. This person will be suitably qualified and experienced and have been authorized to do so by the principal investigator. Once an eligible patient is identified, they or their parent or legal guardian will be approached by a practice GP or research nurse. Written and verbal versions of the participant information and informed consent will be presented to the patient or their parent or legal guardian detailing no less than the exact nature of the study, what it will involve for the participant, the implications and constraints of the protocol, and the known side effects and any risks involved in taking part. It will also be clearly stated that the participant is free to withdraw from the study at any time for any reason without prejudice to future care, without affecting their legal rights, and with no obligation to give a reason for withdrawal.

The patient will be allowed as much time as wished to consider the information and provided the opportunity to question the investigator, their GP, or other independent parties to decide whether they will participate in the study. Written informed consent will then be obtained by means of a dated signature and the dated signature of the person who presented and obtained the informed consent. A copy of the signed informed consent will be given to the participant. The original signed form will be retained at the study site.

When the eligible patient is not able to attend the practice in person, they will be told about the study remotely by a trained GP or nurse. The trained GP or nurse will go through the remote consent form with the participant over the phone. Once the participant has provided verbal consent to take part in the study, the researcher will sign a copy of the remote consent form and will provide the participant with a copy via a secure method such as NHS email. The patient will then be sent a swab to take at home and return to the practice within 4 hours of being taken for immediate POCT. Collection of the sample will be arranged by study staff.

For the ethnographic observations, we will verbally inform and orally consent the clinicians, a PIAMS researcher will record the consent process by completing a Record of Consent Form and the form will be signed in the presence of the participant to confirm oral consent. We will also provide information about the PIAMS study on practice posters to notify the patients about the observation activities associated with the nested qualitative study. Their consent will be implied by not opting out. A PIAMS researcher will be available to answer any questions they may have about observations undertaken for the nested qualitative study. Both clinicians and patients have the right to withdraw from participation or to decline to participate at any time without reason.

For the semistructured questionnaire, all survey respondents will complete an informed consent question embedded at the beginning of the anonymous questionnaire. If the participants answer “YES” to the first question of the form, this will imply their consent to participate, and the survey will begin. If the participants answer “NO” to the informed consent question, they will directly exit the current page. No participant will be forced to participate in the survey, and their participation will be based on their agreement, which can be withdrawn at any time.

Pseudonymized information about swab samples from consented patients, including participant ID, site ID, and swab result, will be stored in the POCT machines. These data will be extracted weekly from the machines and sent via an encrypted email to the study team to be stored in the research group’s secure network.

Data from study practice medical records will be extracted twice weekly from information systems of the RCGP RSC practices by Apollo, part of Wellbeing Software. These records are pseudonymized as close to the source as possible by Apollo using a nonreversible “hash” algorithm. Patients who decline to share their data are excluded from the extraction process.

Data for the study are held on dedicated secure servers at the RCGP data and analytics hub in the Clinical Informatics and Health Outcomes Research Group, University of Oxford. The research group’s secure network is located behind a firewall within the university’s network; all in-bounded connections are blocked, but out-bounded connections are allowed. Only staff members or associated members of the research group approved by the head of department can access the data from secure workstations or secure laptops with encrypted drive. All staff members of the research group working within the team base work from secure workstations or secure laptops with encrypted drive within the research group’s secure network. The use of personal equipment is not permitted and cannot be connected to the secure network. A risk assessment of the physical security of the research group's offices and server room has been conducted by the building and facilities manager, the faculty information technology (IT) service manager, and the research group's information governance lead.

Survey data for the nested qualitative substudy are securely collected using Jisc (online surveys). The university has a license agreement to use this service and has recommended the service for gathering confidential data. Extraction of the survey data is only available to people with a registered Jisc account, which the university has to approve. Only authorized study researchers will be able to export survey data once logged in to Jisc. Once survey data are extracted, the data will be stored within the secure Oxford-RCGP Clinical Informatics Digital Hub (ORCHID) network. Access to your data is strictly controlled. Only authorized study researchers will have access to only pseudonymized research data from within the aforementioned secure ORCHID network.

The university is compliant with the Data Protection Act and UK GDPR and has systems for technical and organizational controls for information security, including a university-level Information Security and Governance Group chaired by the university senior information risk owner. The research group’s private network has its own system-level security policy and is tested for vulnerabilities annually.

Study practices are provided with a fee for participating in this study to cover the costs of training staff and hosting the study. A small remuneration is also provided to practices for each swab taken to cover the additional time taken during each consultation to undertake swabbing for this study. Patients are not remunerated for taking part in this study.

